#### Statistical Analysis

First, we will compare the amount of improvement in the Mini-BESTest with an analysis of covariance (ANCOVA) model, controlling for age. It is possible that lower functioning patients will have larger adaptation to ABC-C since they start out with less function. Alternatively, it is possible that the lower functioning patients will have poorer exercise tolerance so will improve less so we will also control for baseline Mini-BESTest*.* Because we are utilizing a crossover design, the treatment effect will represent change during the ABC-C versus control rehabilitation periods regardless of whether a patient received the ABC-C intervention during period 1 or period 2. We will assess, but do not anticipate, period by treatment group interaction effects. We will also enter an interaction term into the model to assess for differential intervention effects cognitive and/or frontal lobe structural and functional connectivity status. Second, we will relate the percent improvement in the Mini-BESTest with ABC-C intervention with baseline measures of posture/gait impairments, cognitive impairments and both structural and functional connectivity of the Posture/Locomotor circuit at baseline with linear regression models. Previous studies have shown the Minimal Detectable Change of the Mini-BESTest was 3 points [52]. We will also determine how many subjects move from high- to low-fall risk; a cutoff score for identifying PD fallers from non-fallers with the Mini-BESTest is 19/28 (63 %), with a sensitivity of .98 in 80 subjects [53].

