## Methods/design

The study is a cross-over, randomized, controlled trial design to determine responsiveness to the ABC-C exercise program. The study will include 120 people with PD (Fig. 1). People will be randomized into either an exercise (case) or education (control) 6-week intervention period. They will cross over after 6 weeks to receive the other treatment. Both interventions were designed to have the same frequency and will be delivered by the same exercise trainers for all sessions. Preceding the interventions, all patients will be tested on multiple measures of mobility cognition, and imaging. This same battery of tests will be administered after 6 weeks of intervention before the participants cross over into the second intervention. A final assessment will occur at the end of the second and final treatment arm (Table 2). All other interventions (medication, other interventions, exercise) will be kept as stable as possible and any changes in medication will be monitored. This trial is registered at clinical trials.gov (NCT02231073) and OHSU ethics committee has approved all aspects of the study. All research is in compliance with the Helsinki Declarations.

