### Sample Size

We computed power to detect differences between the intervention arms in a crossover trial via analysis of variance with level of significance set to 0.05 (SAS software v9.3). We assumed baseline levels and patterns of change similar to those reported in King 2013 [28]. We examined the significance of treatment effect from 1000 simulated replications of a crossover trial. The trial is comfortably powered (85 %) with 120 patients if total Mini-BESTest score increases by 2.4 points on average in the ABC arm, and only 1.3 points on average in the control arm. We predict a roughly 20 % drop-out rate, which is conservative based on our previous experience with short duration trials of rehabilitation in PD and by others [24, 25, 28, 29].

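### The primary ANCOVA names no within-patient term for two Mini-BESTest changes that share the mid-test; fitted as independent rows or with a random patient intercept, its type I error could reach about 11%

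*Protocol article*

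**What the plan says.** Protocol article, Statistical Analysis: the primary comparison is of improvement, and "we will compare the amount of improvement in the Mini-BESTest with an analysis of covariance (ANCOVA) model, controlling for age". Baseline Mini-BESTest is added because lower-functioning patients may respond more, or less, to exercise. Because the design is a crossover, "the treatment effect will represent change during the ABC-C versus control rehabilitation periods", whichever period ABC-C fell in. Period is mentioned only through a period-by-treatment interaction that will be assessed. No patient, repeated-measures or covariance term is named.

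Protocol article, Methods/design and Assessment procedures: there are three tests. The second is "administered after 6 weeks of intervention before the participants cross over into the second intervention", so it both closes period 1 and opens period 2.

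Protocol article, Sample Size: the authors computed "power to detect differences between the intervention arms in a crossover trial via analysis of variance" at the 0.05 level, without listing the model terms. They put power at 85% with 120 patients. The gains assumed for that figure are worded as follows: "total Mini-BESTest score increases by 2.4 points on average in the ABC arm, and only 1.3 points on average in the control arm". No standard deviation or within-patient correlation is printed; on variability the section says only "We assumed baseline levels and patterns of change similar to those reported in" an earlier study.

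**The concern.** Pooling the periods gives two outcome rows per patient: mid minus baseline, and final minus mid. Any chance error in the mid-test raises one change and lowers the other by the same amount. In one patient, one of these changes belongs to ABC-C and the other to education, so the error enters the treatment contrast twice in the same direction. An analysis that takes the rows as independent does not see this and reports too small a standard error.

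The usual repair, a random patient intercept, does not help when the outcome is a change score. It can represent only positive correlation within a patient; its variance is estimated at zero and the model falls back to independent rows.

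At stake are the width of the confidence interval and the true error rate of the trial's primary test.

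**Working it through.** **Inputs.** From the article: alpha 0.05 (sidedness not stated, two-sided assumed), 120 patients, difference in change 2.4 - 1.3 = 1.1 points, power 85%, drop-out about 20% (96 completers if 120 is the number enrolled), tests at baseline, mid and final. Assumed: 1:1 sequences. The correlation r of the two changes is not in the documents and is varied below.

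**1. The plan's own figure.** The 85% cannot be recomputed without an SD. Solved backwards, the standard error is 1.1/(1.960 + 1.036) = 0.367. With 120 patients this means either
- an SD of the within-patient difference of 0.367 × √120 = 4.02 (error SD 4.02/√6 = 1.64 under step 2), or
- an SD of a single change of 0.367 × √60 = 2.84, if 240 rows were taken as independent.

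The article does not allow a choice between them.

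**2. Correlation.** Let each test be a patient level plus an independent error of variance s². Then Var(change) = 2s², Cov(change 1, change 2) = -s², and r = -s²/2s² = -0.5.

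**3. Standard error and type I error.** With balanced sequences the pooled estimate is the mean of D = change in ABC-C minus change in education.
- True: Var(D) = 2s² + 2s² + 2s² = 6s².
- Under independence: 4s².
- Ratio of standard errors: √(6/4) = √(1 - r) = 1.225.
- Type I error: 2 × [1 - Φ(1.96/1.225)] = 0.1095.

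**4. Dependence on r.** With autocorrelation φ between successive errors, r = -(1 - φ)/2. With patient-specific linear trends of SD k times the error SD, r = (k² - 1)/(k² + 2). The simulated column is an ANCOVA on 240 independent rows from 120 patients, with age and study-entry score as covariates and 4,000 trials per line.

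| Errors | r | Formula | Simulated |
|---|---|---|---|
| Independent | -0.50 | 10.95% | 11.4% |
| φ = 0.3 | -0.35 | 9.2% | 9.3% |
| φ = 0.6 | -0.20 | 7.4% | 7.9% |
| φ = 0.9 | -0.05 | 5.6% | 5.8% |
| k = 0.5 | -0.33 | 9.0% | 9.5% |
| k = 1 | 0 | 5.0% | 5.2% |
| k = 1.5 | +0.29 | 2.0% | 2.4% |

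With independent errors, the simulated rate was 10.6% to 12.0% as the share of variance between patients fell from 0.9 to 0.6. It was 9.2% if the period-specific baseline was the covariate. A separate simulation with 96 patients (baseline SD 4.5 and error SD 1.6, both assumed) gave 10.7% with study-entry baseline, 9.6% with period-specific baseline, and 4.8% when D was analysed by sequence.

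**5. Valid comparison.** Testing the within-patient difference between sequences gave 4.2% to 5.8% in every scenario of the 4,000-trial simulations above.

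**6. Random intercept.** In 2,000 simulated trials of 120 patients with independent errors, the sample correlation of the two changes was negative every time. A variance bounded at zero would therefore be estimated at zero.

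**7. Period term.** With a period effect of one error SD, the independent-rows ANCOVA rejected in 8.3% of trials without a period term and in 12.0% with it. Leaving period out enlarges the residual; it is not the source of the small standard error. It matters for bias: with n1 and n2 completers in the two sequences and a period difference δ in change, the pooled contrast is shifted by δ(n1 - n2)/(n1 + n2), which is zero only if the sequences stay balanced.

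**The case against.** The strongest reply is that this reads silence as a statement. The article is condensed, the analysis plan is not shown, and nothing says that the rows are independent. The stated treatment effect can be read as a within-patient difference, and the power calculation refers to a crossover ANOVA, which ordinarily carries patient and period effects and would be valid.

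Part of this stands. A reader might infer that the plan states an independent-rows model; it does not. A reader might infer that 11% is a property of the plan; it rests on a correlation that the documents do not give. A reader might also blame the missing period term for the small standard error; step 7 shows the reverse, and the planned interaction may bring period into the model anyway. Nor does the article predict different drop-out in the two sequences.

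Two things do not go away. First, the article names the covariates, and they do not fit the standard fixed-patient ANOVA: age and study-entry score are constant within a patient and would be absorbed by the patient effects. Second, the common charitable reading, the same ANCOVA with a random patient intercept, leaves the fault in place. So the problem is more than an unlisted detail: an analyst who follows the text by ordinary practice can reach the anti-conservative test.

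On the covariate, Assessment procedures uses baseline for study entry, so the term is only open to misreading in period 2.

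**Conclusion.** The point holds in conditional form. The named analysis uses pooled change scores that share the mid-test and names no term that would account for it. Fitted as independent rows, or with a random patient intercept on the changes, it can understate the standard error by a factor of up to about 1.22 and run at about 11% two-sided instead of 5%.

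That size assumes r = -0.5, which follows from independent, equal-variance errors. With autocorrelation of 0.3 to 0.9 the simulated rate is 9.3% down to 5.8%. It is nominal when the patient-trend SD equals the error SD and below nominal beyond that.

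A reader might also infer that the stated power is wrong. If the 85% had come from independent rows, the valid test at r = -0.5 would have power Φ(2.996/1.225 - 1.960), about 69%. The documents do not say that it did, so no such claim is made.

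**What to change.** Name one valid analysis in the plan.

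- **Preferred:** one value per patient, D = change in ABC-C minus change in education. Regress D on sequence coded +1/-1, with age and study-entry Mini-BESTest centred at their means. The intercept is the treatment effect, and the sequence term removes any period effect even if the sequences become unequal.
- **Alternative:** model the three visit scores with visit, treatment and an unstructured within-patient covariance. Code treatment as ABC-C completed by that visit, so that its coefficient is the same contrast of changes. This form also uses patients who miss the final test.

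In either case, state that baseline means study entry, and do not use the mid-test as a covariate, because it is measured after period 1 treatment.

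The cost is wording. No data, visits or patients are added. The confidence interval may be wider than the one that an independent-rows analysis would report.

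### The pooled crossover effect also counts any exercise gain lost during the later education period; a fixed period-1 estimate should be reported beside it

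*Protocol article*

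**What the plan says.** The Methods/design section describes two 6-week interventions in randomised order: "They will cross over after 6 weeks to receive the other treatment". The test battery is given before the first intervention, once more before the crossover, and at the end; Assessment procedures lists the same three occasions for the mobility and cognitive measures. Neither section describes a washout interval or a second baseline at the start of period 2.

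Statistical Analysis compares improvement in the Mini-BESTest by ANCOVA, controlling for age and baseline Mini-BESTest, and defines the contrast so that "the treatment effect will represent change during the ABC-C versus control rehabilitation periods regardless of whether a patient received the ABC-C intervention" first or second. The next sentence adds: "We will assess, but do not anticipate, period by treatment group interaction effects".

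Sample Size states: "The trial is comfortably powered (85 %) with 120 patients". The figure assumes a mean Mini-BESTest gain of 2.4 points with exercise against 1.3 with education.

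**The concern.** A trained skill does not return to its starting level on the day training stops. The state at the mid-test therefore carries whatever exercise achieved into period 2 for the exercise-first half. If that gain fades while those patients attend education, the fading is recorded as a poorer change under education, and the pooled contrast credits the difference to exercise.

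The article's first purpose is to find out whether the exercise programme improves mobility and/or cognition compared with education. A pooled number that mixes the six-week effect with what happens in the following six weeks answers a somewhat different question. A reader of the result could not separate the two parts.

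**Working it through.** **Inputs.** From Sample Size: mean gains E = 2.4 (exercise) and C = 1.3 (education); 120 patients; power 85 %; "level of significance set to 0.05" (two-sided assumed); and "We predict a roughly 20 % drop-out rate". The article gives no SD or within-patient correlation: "We assumed baseline levels and patterns of change similar to those reported in King 2013". It gives no fade rate either. Let λ be the share of a gain lost in the following period; every value of λ below is an assumption.

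**The plan's own figure.** The 85 % cannot be reproduced without an SD, so it is inverted. The SD of the within-patient difference of the two changes is 1.1 × √120 / (1.960 + 1.036) = 4.02, and the pooled SE is 4.02/√120 = 0.37. With no fading, the pooled effect is 2.4 − 1.3 = 1.1, as planned.

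**Only the exercise gain fades.** Exercise-first patients contribute E − (C − λE). Education-first patients contribute E − C. With equal sequences the pooled effect is (E − C) + λE/2.

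**Both gains fade at the same rate.** Education-first patients now contribute (E − λC) − C, and the pooled effect is (E − C)(1 + λ/2).

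| Assumed loss λ | Only exercise fades | Both fade equally |
|---|---|---|
| 0 | 1.10 | 1.10 |
| 25 % | 1.1 + 0.6/2 = 1.40 | 1.1 × 1.125 = 1.24 |
| 50 % | 1.1 + 1.2/2 = 1.70 | 1.1 × 1.25 = 1.375 |

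If exercise-first patients instead went on improving by x points after exercise ended, the pooled effect would fall by x/2.

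**Baseline adjustment.** The article does not say which baseline is the covariate. In simulation (between-patient SD 4.5 assumed), adjusting for the study baseline left the inflation unchanged. Adjusting for each period's own baseline lowered the estimate by only about 0.05-0.07 points.

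**The interaction check.** The period-by-treatment interaction equals the difference between sequences in total change over both periods. If only the exercise gain fades, that difference is λE: 0.6 points at 25 % and 1.2 at 50 %.

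- Independent visit errors: the contrast carries six error variances, so the error SD is 4.02/√6 = 1.64. Total change has SD 1.64 × √2 = 2.32, and the SE is 2 × 2.32/√120 = 0.42. Power is about 29 % at 25 % loss (26-31 % in simulation) and about 80 % at 50 %.
- Independent changes: total change has SD 4.02, and the SE is 2 × 4.02/√120 = 0.73. Power is about 13 % and 37 %.

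**Precision of a period-1 comparison.** It targets 1.1 whatever λ is.

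- Independent visit errors, adjusted for baseline (between-patient SD 4 assumed): SE 0.41; 1.1/0.41 = 2.68; power about 76 %. Unadjusted change gives about 74 %.
- Independent changes: SD of one change 4.02/√2 = 2.84; SE 2 × 2.84/√120 = 0.52; 1.1/0.52 = 2.12; power about 56 %.
- If only 96 patients are analysed (120 × 0.8) with the same SDs, the SEs grow by √(120/96) = 1.12. Power falls to about 67 % and 47 % respectively.

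**The case against.** **Fading is not shown.** The article gives no figure for it, and full persistence would leave the pooled effect unbiased. This stands: the inflated values are scenarios. It does not remove the point, because in any case other than full persistence the pooled number includes what followed the first intervention, and the pooled estimate cannot show which case applies.

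**A reader might infer a raised false-positive rate.** If both arms truly gain 1.3, the exercise gain is lost completely and the education gain persists completely, the pooled effect is 1.3/2 = 0.65. With SE 0.37 it would be significant in about 43 % of trials. The documents do not support taking that one-sided extreme as the expected case. With equal true gains and equal proportional fading, (E − C)(1 + λ/2) is exactly zero and the error rate is not inflated.

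**The interaction is already to be assessed.** A model with that term can yield the period-1 effect, and what follows from a positive test may be set out in a fuller document that is not shown. The silence on consequences is therefore not held against the article. What remains is that a non-significant result from so weak a test would not validate the pooled estimate.

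**No washout is an inference** from the schedule, not a statement. That is fair, but an unmentioned gap would not help: the period-2 change would still start from the mid-test before the crossover.

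**A reader might infer that period 1 should replace the pooled primary analysis.** The documents do not compel this. The trial was powered by simulating a crossover, and the loss of power could be as large as 85 % to 56 % before drop-out. Replacement is a trade-off rather than the correction of an error.

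**Conclusion.** The point holds as a conditional one. Because period 2 starts from the mid-test and both orders are pooled, any exercise gain lost during education adds half of that loss to the treatment effect. Under the planned gains, a loss of 25-50 % would turn 1.1 into 1.4-1.7 if only exercise gains fade, and into 1.24-1.375 if both fade alike. The bias is zero with full persistence and negative with continued improvement.

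The direction follows from the stated design. The size rests on assumed fade rates. The power figures rest on an SD inferred from the stated 85 % and on the two error structures shown. The 85 % itself is neither confirmed nor refuted. Adding a carryover-free estimate is a worthwhile, inexpensive improvement; the pooled analysis does not have to be abandoned.

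**What to change.** Keep the pooled crossover analysis as the powered primary. In Statistical Analysis, add three statements:

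1. A randomised period-1 comparison is pre-specified: mid-test Mini-BESTest by assigned first treatment, adjusted for baseline Mini-BESTest and age. It is reported beside the pooled estimate whatever the interaction test shows.
2. The pooled estimate includes any loss (or further growth) of gains made in the earlier period.
3. The interaction test is descriptive and is not used to choose between the two estimates.

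The cost is one extra analysis of data already planned, with no added visits or patients. Its precision is lower: about 56-76 % power for 1.1 points at N=120 under the SD implied by the stated power, and less with drop-out. It should therefore be read as an estimate with its confidence interval, not as a second test that must also succeed.

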Imaging studies also suggest a link between structural and functional changes in the frontal lobe (a region commonly associated with cognitive function) and mobility. A recent European study of 415 older people used diffusion tensor imaging (DTI) to show that parkinsonian signs of slow walking speed, and falls are related to white matter loss in the frontal cortex, but not the basal ganglia [14–16]. Likewise, a recent systematic review that included eighty-six published studies using various imaging modalities to relate neuroimaging to mobility reported that there were consistent finding across imaging modalities linking frontal lobe measures with mobility performance [17]. Specifically, this targeted review supports an increased cortical control of gait in aging, reduced volume in several regions of grey and white matter that relate to impaired mobility and consistent neuroimaging findings that reveal the basal ganglia, parietal and frontal cortices and cerebellum are related to mobility outcomes [17]. Recent work identifying the locomotor neural network, which includes the i) supplementary motor area, ii) subthalamic nucleus, iii) mesencephalic and iv) cerebellar locomotor regions, also provides evidence for reduced structural and altered functional connectivity in people with PD [18, 19].

Though mobility and cognitive function may be related, rehabilitation of such deficits typically remains separate. There is some evidence that cognitive training may improve motor function and that mobility training may improve cognitive function in the elderly but a recent meta-analysis on this topic revealed limited and low quality studies [20]. Although many individual studies of exercise and rehabilitation interventions report success in improving balance and gait in people with PD, the overall effect size of many interventions are sometimes minimal, often not reaching the minimally important change and/or minimal detectable change levels [20–25]. The limited success of rehabilitation treatment for mobility problems in people with PD may be because current physical therapy treatment does not directly address deficits related to frontal cortex dysfunction, such as cognition and cognitive control of balance and gait.

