### Participants

Inclusion criteria for PD recruitment are a) ages 50–90 years old, without major musculoskeletal or peripheral or central nervous system disorders (other than PD) that could significantly affect their balance and gait, b) no recent changes in medication, excessive use of alcohol or recreational drugs, c) no history of structural brain disease, active epilepsy, stroke or acute illness, factors affecting gait such as severe joint disease, weakness, peripheral neuropathy with proprioceptive deficits, severe peripheral vascular occlusive disease, severe musculoskeletal disorders, uncorrected vision or vestibular problems, or dementia that precludes consent to participate or ability to follow testing procedures, d) ability to stand or walk for 2 min with or without an assistive device, e) no medical condition that precludes exercise, f) no claustrophobia, severe tremor, or any health history (implanted devices, Deep Brain Stimulation, etc.) that would interfere or put the subject at risk near the powerful magnetic field of the MRI scanner. Though the majority of participants will have the diagnosis of idiopathic PD a subset of people with frontal gait disorder may be included for pilot data analysis. Participants will also be assessed at baseline on the Montreal Cognitive Assessment as a global screening of cognition. All subjects will be tested at Oregon Health & Science University. All subjects will sign an informed consent and no minors will be included in the study.

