## Discussion

The overarching goal of this study is to determine if cognitive function and frontal brain circuitry deficits predict responsiveness to exercise. Specifically, we are interested in understanding if certain phenotypes that best predict responsiveness to high intensity, short duration agility rehabilitation with a focus on cognition will help guide therapists to identify candidates for therapy and to develop specific therapy for specific types of mobility disabilities from parkinsonism. To date, there are very few studies on cognitive contributions to gait and balance as they relate to rehabilitation, particularly in this challenging population. Currently, physical therapists do not routinely incorporate cognitive challenges for people with PD and furthermore, it is unclear if these patients will benefit from such training.

If we find that executive function deficits and reduced structural and/or functional connectivity of the locomotor circuitry predict poor responses to challenging balance rehabilitation, that supports our hypothesis that frontal (and prefrontal) lobe impairments limits rehabilitation efficacy. If particular impairments of balance and gait improve more than others with ABC-C, this information will be used to improve the ABC-C intervention and will be followed by studies focused on determining which postural domains are most amenable to improvement with rehabilitation. The results from this study will further our understanding of the relationship between cognition and mobility with a focus on brain circuitry as it relates to rehabilitation potential.

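### The moderator and predictor analyses, as described, do not adjust for differential response by age, so an age-driven association could be read as frontal impairment limiting rehabilitation; adding age terms is a cheap improvement

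*Protocol article*

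**What the plan says.** The Statistical Analysis section describes two analyses that bear on prediction of response.

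- **First model.** "First, we will compare the amount of improvement in the Mini-BESTest with an analysis of covariance (ANCOVA) model, controlling for age". Baseline Mini-BESTest is a further covariate. Into this same model the authors will "enter an interaction term into the model to assess for differential intervention effects cognitive and/or frontal lobe structural and functional connectivity status". No treatment-by-age term is named.
- **Second model.** Percent improvement with ABC-C is related to baseline posture and gait impairment, cognitive impairment, and "structural and functional connectivity of the Posture/Locomotor circuit at baseline with linear regression models". Age is not in that list.

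Three other places matter. Eligibility covers "ages 50–90 years old" (Participants). The Background cites a review that supports "increased cortical control of gait in aging, reduced volume in several regions of grey and white matter that relate to impaired mobility". The Discussion says that if executive deficits and reduced connectivity predict poor response, "that supports our hypothesis that frontal (and prefrontal) lobe impairments limits rehabilitation efficacy".

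**The concern.** Whether cognition and brain circuitry predict response to exercise is the question in the title. The Discussion goes beyond prediction: it would take an association as support for a mechanism. That step needs the association not to be explained by something that lies upstream of both the marker and the response.

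Age is the obvious candidate. The eligible range spans 40 years, the authors' own Background ties aging to brain structure and to the control of gait, and the first model treats age as relevant to improvement. If older patients gain less from ABC-C and also have poorer executive function and connectivity, both planned analyses would tend to show that deficits go with poor response even if the deficits themselves have no effect.

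The age adjustment in the first model appears to guard against this. For the interaction term it does not.

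**Working it through.** **Inputs from the Sample Size section.** "The trial is comfortably powered (85 %) with 120 patients"; "level of significance set to 0.05" (taken as two-sided); mean gains of 2.4 and 1.3 points, a difference of 1.1; drop-out of about 20 %, so 120 × 0.8 = 96 completers.

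**Assumptions, because the article gives no figure.** Correlation ρ of age with a marker such as executive function, -0.3 to -0.5. Correlation r of age with the within-patient benefit of ABC-C over education, -0.1 to -0.3. No direct effect of the marker on benefit.

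**1. The plan's own figure.** No SD is stated, so the 85 % power cannot be reproduced independently. Solving backwards for the SD of the within-patient difference at n = 120:

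SD = 1.1 × √120 / (1.960 + 1.036) = 4.02 (3.99 with a t reference).

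I use 4.0. The argument does not depend on it; it only sets the scale in points.

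**2. Why the main effect does not help.** With one row per patient per treatment, age has the same value in both rows. For patients with both rows, the treatment-by-marker coefficient is the slope of the within-patient difference on the marker, and a patient-constant main effect drops out of that difference. In a simulated two-row data set the coefficient was 0.2223 both with and without the age main effect. It fell to 0.026 once treatment-by-age was added.

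**3. Size for the moderator term, n = 96.** The correlation that the marker acquires through age is ρ × r. The expected z is about ρ × r × √96, with √96 = 9.80. The chance of p < 0.05 is Φ(-1.96 + z) + Φ(-1.96 - z).

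| r | ρ | ρ × r | z | approximation | simulation (4000 runs) |
|---|---|---|---|---|---|
| -0.1 | -0.3 | 0.03 | 0.29 | 6.0 % | not run |
| -0.1 | -0.5 | 0.05 | 0.49 | 7.8 % | not run |
| -0.2 | -0.3 | 0.06 | 0.59 | 9.0 % | 9.3 % |
| -0.2 | -0.5 | 0.10 | 0.98 | 16.5 % | 17.3 % |
| -0.3 | -0.3 | 0.09 | 0.88 | 14.3 % | 14.2 % |
| -0.3 | -0.5 | 0.15 | 1.47 | 31.2 % | 30.6 % |

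With treatment-by-age in the model, the simulated rate was 4.7-5.3 %.

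The slope acquired through age is ρ × r × 4.0 points per SD of the marker: 0.12 to 0.20 points at r = -0.1, and 0.24 to 0.60 at r = -0.2 to -0.3. The latter is 0.24/1.1 = 22 % to 0.60/1.1 = 55 % of the planned difference.

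**4. A separate simulation with smaller age effects included, n = 96, 2000 runs per cell.** Response to ABC-C changes by 0.5 or 1.0 points per SD of age, and the age-marker correlation is 0.3 to 0.5 in size.

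| Analysis | without the age term below | with it |
|---|---|---|
| Moderator model, age as main effect (term added: treatment-by-age) | 6.7-24.6 % | 4.5-5.4 % |
| Regression of raw change with ABC-C (term added: age) | 8.2-38.4 % | 4.5-5.9 % |
| Regression of percent change with ABC-C (term added: age) | 7.8-34.8 % | 4.9-5.2 % (four corner cells, 4000 runs) |

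Leaving age out of the moderator model altogether gave 6.5-23.9 %, almost the same as with the main effect. With either link set to zero, all rates stayed at about 5 % (4-6 %).

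**5. Cost in precision.** Adjusting for age multiplies the standard error of the marker's slope by about 1/√(1 - ρ²): 1.05 at 0.3, 1.09 at 0.4, 1.15 at 0.5.

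**The case against.** **Silence in a condensed article.** The second analysis gets one sentence, and its covariates may be set in a full plan. That age enters as a main effect is inferred. Had the ANCOVA been run on within-patient differences, an age covariate would itself be the treatment-by-age term. This stands in part. The two-row layout is the more natural reading, because in a model of differences a moderator would be an ordinary regressor and not an interaction. But the article does not fix the layout, so the point is an improvement to make explicit, not an error of fact.

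**The marker would still predict.** A reader might infer that the plan produces false predictors with an inflated type I error. The documents do not support that. If executive function tracks age and age governs response, executive function does predict response, and choosing candidates for therapy on it could work. The percentages above count as errors only for the mechanistic sentence in the Discussion. This stands in full.

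**The size is assumed.** It is. At SD 4.0, correlations of -0.2 to -0.3 mean 0.8 to 1.2 points of benefit lost per SD of age, or 73 % to 109 % of the planned 1.1 points. Those are strong effects. The Background links aging to brain volume and gait control, not to response to exercise. At -0.1 the rate is only 6-8 %.

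**Why age alone?** The same algebra applies to baseline Mini-BESTest, the one response modifier that the section discusses, and to disease severity. True, and it is a reason to consider a treatment-by-baseline term too. Age remains a clear case: the section names it as a covariate in one analysis and not in the other, and it cannot be a consequence of cognition or connectivity, so adjusting for it does not remove part of their effect.

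**Conclusion.** The point holds as a cheap improvement to the title question. As described, neither analysis can separate response that varies with age from response that varies with frontal impairment, yet the Discussion would read the result as the latter. The error would be one of attribution, not of prediction.

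It arises only if age both modifies response to ABC-C and correlates with the marker, and the article quantifies neither. For the moderator term the chance per predictor therefore runs from 5 % (either link absent), through about 6-8 % (weak age modification), to 9-31 % (strong age modification), for age-marker correlations of 0.3 to 0.5 in size and 96 completers. The conclusion also rests on the ordinary reading of the age adjustment as a main effect. The randomised comparison of ABC-C with education is not affected.

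**What to change.** In the Statistical Analysis section:

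1. Enter a treatment-by-age term beside each treatment-by-cognition and treatment-by-connectivity term.
2. Include age in each regression of percent improvement on baseline predictors.
3. Report age-adjusted and unadjusted slopes side by side. Rest any statement that the data support the frontal-impairment hypothesis on the adjusted slopes, and use the unadjusted ones for pure prediction.

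A term for randomised sequence may be wanted for period effects, but it is no remedy here: sequence is randomised and so is independent of baseline age and cognition.

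The cost is one model term per analysis, from data already collected, and a standard error about 5-15 % larger for the adjusted slope when age and marker correlate at 0.3 to 0.5. No change to sample size or to the primary analysis is needed.
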